### Instruments and outcome measures

3.3

#### Primary outcome measures

3.3.1

The primary outcome measure is the weekly assessed credibility of idiosyncratic beliefs. These beliefs are evoked by a semi-structured procedure during the baseline phase. Each participant formulates three to five idiosyncratic, dysfunctional beliefs they consider to be central to their personality disorder. Participants will rate the degree they believe each statement on a visual analog scale (VAS) from 0 to 100% credibility. The core beliefs are rated weekly during baseline, treatment and follow-up phases, at the start of each session. The therapist will not be present when participants fill in the VAS to assure integrity. Filled-in forms will be given to the therapist in a closed envelope and passed on to the research team.

#### Secondary outcome measures

3.3.2

*Quality of life* is assessed by the Dutch brief version of the World Health Organization Quality of Life (WHOQOL-BREF; [34]). The WHOQOL-BREF is a self-report measure that consists of 26 items, which are rated on a 5-point Likert scale. Research in two samples of older adults, with mean ages of 73 and 76 years, showed good reliability and satisfactory construct validity [35].

*Psychological distress* is measured by the Brief Symptom Inventory* (BSI; [36]). The BSI is a 53-item self-report measure, which is rated on a 5-point rating scale. The reliability and validity of the BSI are good, with reliability coefficients ranging from 0.68 to 0.91 [37], and the Dutch version of the BSI has been validated in older adults [38].

*Early maladaptive schemas* are measured with the Dutch Young Schema Questionnaire* (YSQ; [39]). The questionnaire consists of 16 subscales and includes 205 items, which are phrased as negative core beliefs and rated along a 6-point Likert scale. In a clinical sample with a mean age of 33.9 years (range 18–74) the YSQ showed good reliability and convergent and discriminant validity [40]. The YSQ measures EMS scales equally across age [41].

*Schema modes* are assessed by the Dutch Short Schema Mode Inventory* [42]. It consists of 14 subscales and includes 118 items which must be rated on a 6-point Likert scale. This questionnaire has acceptable internal consistencies (Cronbach α′s from 0.79 to 0.96) and moderate construct validity [42].

*Current severity of BPD* is assessed with the Dutch version of the BPDSI [43], a semi-structured interview which assesses the frequency and severity of BPD symptoms during the last three months. The BPDSI consists of nine sections, one for each of the DSM-criteria for BPD and appears reliable and internally consistent [43].

*Personality Disorder Diagnoses* are assessed with the SCID-5-P* [28], a semi-structured interview for DSM-5 personality disorder diagnoses. Personality disorder-criteria are rated on a 3-point scale as absent, sub-threshold or threshold. Reliability and validity are not yet available, but are expected to be similar to the Dutch version of the Structured Clinical Interview for DSM-IV Axis II disorders [44] as both instruments are almost similar. Inter-rater agreement appeared excellent in adults with an average age of 35.5 years (range 18–61), with a mean value of Cohen's kappa of .84 [45].

*Personality functioning* is measured with the Severity Indices of Personality Problems short form* (SIPP-SF; [46]), a self-report questionnaire aiming to measure the severity of the generic and changeable components of personality disorders. The SIPPF-SF consists of 60-items and five domains: self-control, identity integration, responsibility, relational capacities, and social concordance. Participants are asked to answer on a 4-point scale to what extent they agree with the statement presented, referring to the past three months. A study concerning the construct validity of the SIPP-SF for older adults demonstrated a structure of five higher order domains of personality functioning [13].

*Dimensional assessment of pathological personality traits:* The Personality Inventory for DSM-5* is a 220-item self-report questionnaire developed to assess personality traits in line with the dimensional perspective of personality pathology as advocated in Section-III of DSM-5 [47]. The original five-factor structure of the PID-5 has been confirmed in the Dutch version, and it has adequate reliability and convergent and discriminant validity [29].

These secondary outcomes will be measured four times: at the start of treatment and after six, twelve, and eighteen months, except for the SCID-5-P which will be administered twice (before and directly after the treatment phase).

### Ethical issues and treatment integrity

3.4

The study procedure was reviewed and approved by the internal ethical committees of Breburg and Mondriaan, and METC Brabant, an independent ethical committee. All participants will be informed by the principal investigator, both orally and by letter, and sign an informed consent before the start of the study. Most of the measures used for inclusion and study outcomes are a standard part of routine outcome monitoring and standard diagnostic procedures at Breburg and Mondriaan (these measures are marked with an asterisk [*]). Two diagnostic instruments are added to this standard battery: the World-Health-Organization-Quality-Of-Life, brief version (WHOQOL-BREF, which measures quality of life) and the Borderline Personality Disorder Severity Index (BPDSI, which assesses the frequency and severity of BPD symptoms). ST can be considered a safe treatment as it has been found effective for BPD in younger adults, and it is increasingly used as a treatment in older adults in clinical practice; moreover, the effectiveness of ST has been established in older adults with cluster C personality disorders [21].

Treatment integrity is secured in five ways. All therapists in this study are well trained and educated in ST and are (candidate) members of the Dutch schema therapy association. Second, therapists can consult each other. Third, all therapists receive a training in which the study design and ways of reporting the sessions are made explicit. Furthermore, each session is registered using a tailor-made session registration form to describe the applied ST intervention. And finally, a random sample of five recorded sessions per therapy is rated for adherence to ST, using the Schema Therapy Rating Scale [48].

## Statistical and power analysis

4

A multiple baseline design is, just like an RCT, capable of demonstrating the occurrence of change over time as a result of an intervention [49]. The fact that participants serve as their own controls and that the primary outcome is measured frequently can compensate for the potential loss of power. As an indication, it is possible to detect a large effect size (d > 1.5; power > .80) with four participants with twenty measurements each [24]. Due to the design of the current study, it is to be expected that the number of participants and measurements necessary to obtain such power will be exceeded.

Statistical analysis will be performed using a time series analysis based upon mixed regression. This type of analysis is possible because of the sufficient length of the treatment phase [25,26]. Mixed regression analysis will be used to explore the differences between treatment and the follow-up phase compared to the baseline phase.

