### Study design and procedure

3.1

This study is a multiple baseline case series design [24]. We chose this design for several reasons. A multiple-baseline case series design offers experimental control over time versus intervention effects, which is an important advantage over an open trial. Like an RCT, a multiple-baseline design can demonstrate significant change and that this change is the result of the intervention and not of time [25]. Secondly, an advantage of this design over a randomized controlled trial (RCT) is that this design requires fewer participants; participants act as their own controls, thus increasing power [26].

A multiple-baseline design requires a dependent variable that is frequently assessed and highly sensitive to change, in order to assess the time and intervention effects [25]. Such a variable should represent a core aspect of the disorder that is addressed by the treatment. The frequent assessments make it possible to distinguish time from treatment effects and allow that each case is its own control. In other words, the frequent assessments of the central variable compensate for the small number of participants. As central variable, we chose the strength of belief participants have in their personal core beliefs, which they view as central to their PD problems. This idiosyncratic measure represents the EMS that are assumed to underlie the patient's personality disorder problems according to the schema therapy model [16].

The design consists of three phases. First, a baseline phase varying in length from four to eight weeks. No therapeutic interventions will be applied during this phase. The second phase is the treatment phase and consists of ST for BPD according to the model of Young and colleagues [17]. Precise methods for the treatment of BPD using ST is described in Arntz & van Genderen [27]. The third and final phase is a six months follow-up with monthly booster sessions.

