The length of the baseline phase is randomized across participants to increase the internal validity. Randomization of participants over variations in baseline length increases the experimental control over differentiating time from treatment effects. Baseline varies between four to eight weeks and will be randomly assigned by an independent colleague using a lottery system. The lottery system consists of five different possible outcomes (4, 5, 6, 7, and 8 weeks). Each different outcome is represented two times, making a total of ten outcomes. There is no replacement after each draw, so different baseline lengths are evenly distributed among participants.

The duration of the treatment phase is 52 weeks and is estimated to be sufficient to accomplish meaningful results [21]. During the treatment phase, the therapist decides when to introduce the different techniques, according to the ST model [16,27] and participants’ case conceptualization.

The follow-up phase lasts six months and includes monthly booster sessions in which the aim is to maintain the acquired ST knowledge and skills.

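### The stated contrast of treatment and follow-up with baseline cannot by itself show that change is due to schema therapy rather than time, and no stated analysis exploits the randomised start points

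*Protocol article*

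**What the plan says.** Section 3.1 (Study design and procedure) justifies the design by what it can attribute: "Like an RCT, a multiple-baseline design can demonstrate significant change and that this change is the result of the intervention and not of time". It gives the same reason for randomising baseline length: "Randomization of participants over variations in baseline length increases the experimental control over differentiating time from treatment effects". Allocation is by lottery without replacement: "The lottery system consists of five different possible outcomes (4, 5, 6, 7, and 8 weeks"), each length drawn twice, for ten participants. Treatment then runs for 52 weeks and follow-up for six months.

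The primary outcome (section 3.3.1) is the credibility of each participant's own core beliefs on a 0 to 100% scale, rated weekly in all three phases.

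Section 4 (Statistical and power analysis) announces a mixed-regression form of time series analysis and then names its comparison: "Mixed regression analysis will be used to explore the differences between treatment and the follow-up phase compared to the baseline phase". It mentions no time, slope or phase-by-time term, and no test that uses the lottery. It does not say that time is left out either.

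**The concern.** Within every participant, baseline comes first, treatment second and follow-up third. A difference between phases is therefore also a difference between earlier and later. Natural improvement, regression to the mean after entry, or habituation to weekly rating of the same statements would all appear as a difference from baseline. A multiple-baseline design guards against this through the staggered start, when some participants are treated while others are still waiting. If the analysis neither models time nor uses the stagger, the result is pre-post change in ten people. The claim at stake is the one for which the design was chosen over an open trial.

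**Working it through.** **The plan's own figure.** Section 4's only figure is a power indication: d > 1.5 with power above .80 from four participants with twenty measurements each. Autocorrelation and test are not given, so it cannot be reproduced exactly. Treating it as 40 against 40 observations gives power above 0.999 if independent, 0.918 at AR(1) 0.6 and 0.609 at AR(1) 0.8. It is plausible, and the planned 580 ratings (60 baseline + 520 treatment) exceed 80. But it concerns power, not attribution, and the point does not depend on it.

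**Time gap between phases** (inputs from section 3.1). For baseline length b, with weeks counted from 0, mean baseline time is (b − 1)/2 and mean treatment time is b + 25.5.
- Treatment minus baseline: b/2 + 26. With mean b = 6 this is 29 weeks.
- Follow-up minus baseline, assuming 26 weekly ratings: b/2 + 65 = 68 weeks.
- Share of a yearly linear drift absorbed by the treatment contrast: 29/52 = 56% with unweighted means, and about 51% in a mixed model with AR(1) 0.3.

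**Concurrent control from the stagger.** Treated participants in weeks 5, 6, 7 and 8 number 2, 4, 6 and 8, a total of 20. Treated person-weeks total 10 × 52 = 520, and 20/520 = 3.8%. From week 9 everyone is in treatment.

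**Consequence if the model had phase terms only.** The documents give no drift, SD or autocorrelation, so these are assumptions shown as a range. There is no treatment effect in any row; nominal error is 5%.

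Test A: t-test on ten per-person phase differences, residual SD 1. Repeat runs differ by one or two percentage points.

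| Drift per 52 weeks | Spurious effect | Significant, independent | Significant, AR(1) 0.3 |
|---|---|---|---|
| 0 | 0 | about 5% | about 5% |
| 0.5 SD | −0.28 SD | 43% | 30% |
| 1.0 SD | −0.56 SD | 93% | 81% |
| 1.5 SD | −0.84 SD | 100% | 98% |

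Test B: mixed model with random intercept and AR(1) 0.4, within- and between-person SD 15 points.

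| Decline per week | Same in SD per 52 weeks | Phase only: effect, significant | With linear time: significant |
|---|---|---|---|
| 0 | 0 | about 0, 5.8% | 5.4% |
| 0.1 points | 5.2/15 = 0.35 | −2.6 points, 15.8% | 4.9% |
| 0.2 points | 10.4/15 = 0.69 | −5.1 points, 45.8% | 4.6% |
| 0.4 points | 20.8/15 = 1.39 | −10.1 points, 95.5% | 5.4% |

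**What time adjustment costs.** In Test B the SE of the treatment step rises from 2.74 to 3.11 points with linear time (3.11/2.74 = 1.14) and to 4.86 with phase-specific slopes (4.86/2.74 = 1.77). The stagger contributes almost nothing here: the SE with linear time is 3.108 with the lottery lengths and 3.103 with a fixed six-week baseline. The adjustment works through the time course within phases.

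**What it can detect.** Take a true benefit that builds linearly to 1.5 SD over 52 weeks, with no drift.
- Step plus common linear time, fitted to baseline and treatment ratings: the step is estimated at +0.07 SD and time takes −1.49 of the −1.5.
- Separate slopes: the slope-change SE is 3.3 to 3.7 SD per year at low autocorrelation. In Test B it is 1.144 points per week, or 1.144 × 52/15 = 4.0 SD per year. A change of 1.5 SD is about 0.4 SE.
- Randomisation test on weeks 1 to 12 (one-sided, AR(1) 0.3): power is 96% for an abrupt 1.5 SD step and 71% for 1.0 SD, but rejection is 4% for the gradual benefit. Its size is about 5% with no drift and 6% with a drift of 1.5 SD.

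**The case against.** A reader might infer that section 4 commits the trial to a model without time, so that any spontaneous decline will be credited to therapy. The documents do not support that. The same section calls the method a time series analysis, which naturally admits time terms. Section 3.1 says that frequent ratings serve to distinguish time from treatment. The Introduction reports linear trends by phase in the predecessor study with this design. Model terms are also something a condensed article may leave to a fuller document.

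A reader might also infer that the randomised baseline lengths go unused. That is too strong: they set the week in which each participant's phase indicator switches. What is absent is a stated analysis that draws its inference from them.

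The false-positive rates depend on an assumed drift. The article gives reasons to expect little: it describes the disorder as lifelong and schemas as enduring, and the predecessor showed no significant trend in baseline or follow-up. However, 4 to 8 baseline points per person say little about a slow trend, as the slope SEs above show.

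Finally, resting the treatment claim on time-adjusted terms alone could defeat the trial. The predecessor's change was a linear trend during treatment, the pattern those terms can hardly detect. This objection stands and shapes the fix.

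**Conclusion.** The point holds for the contrast as stated. Comparing later phases with baseline cannot alone support the claim in section 3.1 that change is due to the intervention and not to time. The mean gap is 29 weeks, only 3.8% of treated person-weeks have an untreated comparator, and about half of any yearly drift enters the estimate. The error rates of about 30% to 100% apply to a phase-only analysis under an assumed linear drift of 0.5 to 1.5 SD per year; with no drift the rate is about 5%. They do not predict what the trial will report, because the text leaves room for time terms. There is also a limit that no analysis wording removes: with this short stagger, a benefit that builds gradually cannot be firmly separated from time.

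**What to change.** In section 4, or in the analysis plan before the data are analysed:

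1. Keep the treatment-versus-baseline and follow-up-versus-baseline contrasts, and describe them as uncontrolled within-person (pre-post) change.
2. Add, as a supporting analysis, the mixed model with weeks since first rating as a common time term, and report the baseline and treatment-phase slopes with intervals.
3. Add a randomisation test that re-draws the lottery, with 10!/(2!)^5 = 3,628,800/32 = 113,400 equally likely allocations, on an early window fixed in advance, such as weeks 1 to 12.
4. Limit the statement that change is not due to time to what items 2 and 3 support.

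The cost is analysis work and a more modest claim; no new data are needed. The SE of the step rises by about 14% with linear time in Test B (18% with independent residuals, 0.137 to 0.161 SD) and by about 77% with phase-specific slopes. The plan should state the downside openly: items 2 and 3 detect an abrupt change at treatment start but have almost no power for gradual benefit, so they should not replace the phase contrast as the sole test.

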## Discussion

5

To our knowledge, this is the first empirical study of the effectiveness of psychotherapeutic treatment for BPD in older adults. In recent years there has been a shift in thinking about treatment possibilities in older adults with personality disorders [50]. Therapeutic nihilism has been replaced by a more optimistic and promising view that psychotherapy can make a difference for older adults who suffer from personality disorders and that it is possible to enhance their quality of life and sense of meaning in life. The treatment of BPD in younger adults has been examined extensively in the past quarter of a century, but there is still a world to discover in treating BPD in older adults. This study is a first step in the road ahead.

As stated, it is not straightforward to diagnose BPD in older adults. It is a challenging procedure because of the different manifestation of BPD in later life, and the fact that the DSM-description of BPD-traits might lead to an underestimation of the ‘true’ prevalence of BPD at older age. We have also employed a more dimensional model of BPD, in which, besides section II DSM-5 criteria, the pathological personality traits of the alternative model for personality disorders in section III of DSM-5 are used to diagnose BPD in older adults, for cases that are subthreshold BPD according to the criteria of section II of DSM-5. This diagnostic approach is not yet common in studies into BPD in younger age groups, but we think this is helpful to achieve comprehensive and meaningful results in studying BPD in later life.

A possible limitation of the present study is the length of treatment, which is set at 52 weekly sessions, followed by six monthly booster sessions. There is a great variation in the treatment dosage among different studies concerning ST and personality disorders, with the number of treatment sessions ranging from 78 up to 300 sessions [19,20,51]. The length of treatment in the present study is based on the fact that more recent studies show a reduction in length of treatment compared to earlier studies [19,52], and 52 sessions appeared effective in older adults with cluster C personality disorders [21].

A possible criticism could be the small sample size (*N* = 10), in particular compared to RCT studies. Yet the construction of a multiple baseline design makes it possible to acquire sufficient power to demonstrate treatment effects, even with a small *N*.

The results of this study will contribute to our understanding of treating BPD in older adults with ST and intends to provide beneficial information for the development of therapeutic interventions for older adults with BPD.

## Trial status

The trial started in August 2018 and data collection is expected to continue until September 2020.
